#### Indices

The following indices will be created by calculating mean scores: positive and negative traits that are uniquely human (positive and negative stereotypes; two items each) or shared with animals (dehumanization; four items); negative affect (three items); as well as willingness for intergroup contact (four items).

### Analysis plan

#### Data exclusion

We will exclude data from all participants who did not fully complete the study, failed either the attention or the manipulation check, or who indicated that they themselves had ever committed a violent crime or describe themselves as a person with a physical disability.

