### Design plan

To assess the hypotheses, we will conduct a single-blind (online) experiment; participants will not know to which condition they were assigned but researchers will be aware of the respective treatments when analyzing the data. We will apply a between-subjects design that includes two factors (i.e., target group x descriptor) with two levels respectively (target group: people who have a physical disability, people who have committed a violent crime; descriptor: identity-first, person-first) as well as a control group. Simple randomization will be implemented to assign participants.

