#### Data collection procedure

Participants will provide informed consent through a tick-box. Data will be collected on the online opt-in access panel Prolific Academic. Participants will self-identify by responding to an invitation on the platform and will receive reimbursement of 0.50 GBP, corresponding with the anticipated study duration of five minutes. A pre-test, which will capture attitude importance, will be conducted one week before the main study.

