An attention check will be embedded in the list of aforementioned items (‘This is an attention check. Please answer ’Not at all’ to indicate that you pay attention.’). Lastly, participants will be asked to complete a manipulation check (‘You have just answered several questions about a specific group of people. How was this group referred to?’ Answer options: Violent criminals, People with a physical disability, Most people, The physically disabled, People who have committed a violent crime, My friends) and indicate whether they themselves have ever committed a violent crime (No/Yes) or describe themselves as a person with a physical disability (No/Yes).

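### Excluding participants who fail to recall their assigned label conditions the confirmatory contrasts on a post-randomisation response to the treatment

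*Protocol article*

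**What the plan says.** The Design plan assigns participants to a 2 x 2 design plus a control group: "Simple randomization will be implemented to assign participants". Under Manipulated variables, the only thing that differs between the two descriptor arms of a target group is the label used when the outcome items are presented.

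Under Measured variables, the outcomes come first. Then: "Lastly, participants will be asked to complete a manipulation check". The question reads "You have just answered several questions about a specific group of people. How was this group referred to", and the choices are "Answer options: Violent criminals, People with a physical disability, Most people, The physically disabled, People who have committed a violent crime, My friends". In the same closing block participants "indicate whether they themselves have ever committed a violent crime (No/Yes") and answer a similar question on physical disability.

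The Data exclusion section then drops non-completers and those who "failed either the attention or the manipulation check, or who indicated that they themselves had ever committed a violent crime". A yes to the disability question leads to exclusion as well. The rule is unconditional and precedes the confirmatory analyses. The article names no other analysis set for the ANOVAs.

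**The concern.** Randomisation makes the five groups comparable at assignment. An exclusion that depends on something the assigned label can influence may undo that.

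The recall item is such a variable. It is measured after exposure and after the outcomes, and it asks about the treatment itself. A participant who remembers the right group but the other wording is counted as a failure. That near-miss is possible in all four descriptor arms but not in the control arm, and it need not be equally common for a short noun label and a longer person-first phrase.

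If those who fail also differ in their views of the group, the retained arms differ even when language has no effect. Three results would be affected:
- the planned person-first versus identity-first contrast in each descriptor pairing;
- the comparisons with control, which is part of every ANOVA;
- Hypothesis 2, because its equivalence bounds are taken from the effect sizes observed in the disability pairing. Bias there moves the bounds, and bias in the crime pairing moves the difference being tested.

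**Working it through.** **Inputs from the article.** N = 681, α = .01, power .95, f = .175 (Sample size); five arms (Design plan, Table 1); a cited crime-language effect of d = .21 (Generalizing the person-first language effect).

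**The plan's own figure.** A one-way ANOVA with three groups, non-centrality N·f², needs 679, or 681 in equal groups (power .951). The stated N reproduces, so this point does not rest on an arithmetic error. It is used here only for arm size: 681/5 ≈ 136.

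**Where failure can arise, from the answer options.**

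| Arm | Same-group counterpart among the options? |
|---|---|
| Violent crime, identity-first | yes |
| Violent crime, person-first | yes |
| Physical disability, identity-first | yes |
| Physical disability, person-first | yes |
| Control | no; only 'My friends' is loosely similar |

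The running text under Manipulated variables gives the disability person-first label in a 'who have' form, while Table 1 and the answer option use the 'with' form. If the former were shown, the exact label would be missing from the options in that arm. Table 1 suggests that it will not be, but the wording should be made uniform.

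**Illustration of size.** The article gives no failure rates and no link to outcome, so both are assumed. Suppose a latent tendency to fail is correlated ρ with the outcome, in the same direction in both arms, language has no true effect, and a fraction e of an arm is excluded. The mean of those retained shifts by

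ρ · h(e), with h(e) = φ(Φ⁻¹(e)) / (1 − e).

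This gives h(.05) = .109, h(.10) = .195, h(.20) = .350, h(.30) = .497. The spurious difference is b = ρ[h(e₂) − h(e₁)]. With 136(1 − e) retained per arm, SE = √(1/n₁ + 1/n₂), and the two-sided error at nominal .01 is Φ(−2.576 + b/SE) + Φ(−2.576 − b/SE).

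| Excluded in the two arms | b in SD, ρ = .1 to .5 | Type I error at nominal .01 |
|---|---|---|
| 5% vs 5% | 0 | .010 |
| 2% vs 5% | .006 to .030 | .010 to .012 |
| 5% vs 10% | .009 to .043 | .010 to .015 |
| 5% vs 15% | .017 to .083 | .011 to .028 |
| 5% vs 20% | .024 to .121 | .011 to .050 |
| 10% vs 30% | .030 to .151 | .012 to .071 |

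Last row at ρ = .5: b = .5 × (.497 − .195) = .151; n = 122.4 and 95.2; SE = .137; b/SE = 1.10; error ≈ .071.

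**Cross-check without the latent model.** If failers lie g SD from those retained, the shift in an arm is e·g. With 20% vs 5% and g = .5: .20 × .5 − .05 × .5 = .075 SD. If g is measured from the arm mean, the shift is e·g/(1 − e): .125 − .026 = .099 SD. Both lie within the range above.

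**Equal rates alone do not suffice.** If 10% fail in each arm but the correlation is +.3 in one and −.3 in the other, the difference is .3 × .195 + .3 × .195 = .117 SD. The bias vanishes when the mechanism is the same in both arms, or when failure is unrelated to outcome.

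**The case against.** The rule is prespecified, identical in every arm, and aimed at people who noticed the wording, a recognisable target for a study of wording effects. Failure may also be rare: the survey lasts about five minutes, and the affect and contact items presumably repeat the label. The 2% vs 5% row shows that the harm would then be slight. This stands as a limit on size. Prespecification, however, does not restore comparability, and people who register the wording in one arm need not resemble those who do so in another.

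The remedy could be called inconsistent, since completion and the attention check are also post-randomisation. That is true in principle. The difference is that the correct attention-check answer is the same in every arm and does not depend on the label. Counts by arm are still worth giving.

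A reader might infer that the self-description exclusions are equally suspect because they too follow exposure. The documents do not support this. Past violent crime and physical disability are largely fixed before the survey, the article gives no reason why a label would change the answers differently by arm, and removing ingroup members defines the population for hypotheses about outgroups. A disability item phrased alike in every arm does not by itself create a difference between arms.

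A condensed article may also leave by-arm counts and sensitivity analyses to a fuller plan. Their absence is not the point here; the stated exclusion rule is.

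**Conclusion.** The point holds for the manipulation check. The confirmatory ANOVAs are restricted by a response to the treatment, so the person-first versus identity-first contrasts, the control comparisons and the Hypothesis 2 bounds can be biased. The .01 to .15 SD range (type I error up to about .07) rests wholly on the assumed rates and correlations. Its upper end would be sizeable next to the cited d = .21; its lower end would not matter.

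Two stronger readings should be resisted. One is that the rule will produce a false person-first benefit because hostile participants in that arm misrecall the label. Identity-first participants could equally choose the politer option, and the article settles neither direction. The other is that the bias is known to be large. Assuming 30% vs 5% failure and a gap of .8 SD gives .30 × .8 − .05 × .8 = .20 SD, or about .30 SD with the gap measured from the arm mean (.343 − .042), but nothing in the article supports those inputs.

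**What to change.** Amend the Data exclusion section before data collection:
- **Primary set:** all randomised completers who pass the attention check, analysed as assigned whatever their answer to the manipulation check. Use the same set for the Hypothesis 2 bounds and tests.
- **Reporting:** manipulation-check failures by arm, separating choice of the counterpart label from other errors.
- **Sensitivity analysis:** repeat the analyses without those who fail the manipulation check.
- **Self-description exclusions:** keep them as the definition of the outgroup population, with counts by arm because the items follow exposure. Moving them to the earlier survey ("A pre-test, which will capture attitude importance, will be conducted one week before the main study") is not advised. It would single out the two target topics that the filler topics are there to mask.

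The cost is a change of wording and some dilution from participants on whom the label did not register. If 10% failed and language had no effect on them, a true d of .21 would appear as .9 × .21 = .19; at 20%, as .8 × .21 = .17. The sensitivity analysis gives an indication of how much this matters.

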#### Missing data

All questions will require responses, such that no missing data will occur. Incomplete responses will be removed (i.e., listwise deletion).

#### Confirmatory analyses

We will test for median absolute deviation to detect potential univariate outliers for all outcome variables [49]. We do not plan to exclude outliers but will report their presence. Mean scores and standard variations of as well as bi-variate correlations between all measures will be calculated.

Examining Hypothesis 1a-e (i.e., the effects of person-first language), we will test the assumptions for univariate analysis of variances (ANOVA) for all five outcome measures separately for each of the two descriptor pairings (see Huang [50] who suggests multiple ANOVAs with p-values that are corrected for multiple comparisons rather than a multivariate analysis of variance). Once assumption checks confirmed the suitability of the tests, we will conduct five two-tailed ANOVAs, comparing the indices of positive and negative stereotyping, dehumanization, negative affect, and approach behavior intentions between the identity-first, person-first, and control condition regarding the descriptor pairing “people with a physical disability/the physically disabled”. The analyses will then be repeated for the descriptor pairing “people who have committed a violent crime/violent criminals”. Planned contrasts will be used to investigate for each descriptor pairing whether average negative outgroup perceptions and affect are lower, positive perceptions and approach behavior intentions are higher in the person-first as compared to the identity-first language condition. It is further expected that negative outgroup perceptions and affect are lowest as well as positive perceptions and approach behavior intentions are highest in the control condition. Effect sizes and confidence intervals will be computed. To correct for the multiple ANOVAs in each descriptor pairing, p-values are adjusted using the Bonferroni correction. We address concerns about the reduced power of the tests by using the corrected p-value of p = .01 (i.e., .05 divided by five) in the a-priori power analysis (see above).

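### The Hypothesis 1 tests depend on passing assumption checks with no fallback named; an unequal-variance contrast by default would remove the need for the checks

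*Protocol article*

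**What the plan says.** Under Confirmatory analyses, the protocol article tests the ANOVA assumptions "for all five outcome measures separately for each of the two descriptor pairings", which makes ten analyses. The five ANOVAs in each pairing are then to be run "Once assumption checks confirmed the suitability of the tests". It does not say what happens if the checks do not confirm suitability.

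Each ANOVA compares the indices "between the identity-first, person-first, and control condition". The comparison that decides Hypothesis 1 is narrower: "Planned contrasts will be used to investigate for each descriptor pairing" whether outcomes are better "in the person-first as compared to the identity-first language condition". No error term is given for that contrast, and no Welch, robust or separate-variance version is mentioned. The level per outcome is .01, from .05 divided by five.

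Under Design plan, allocation is by simple randomization and "researchers will be aware of the respective treatments when analyzing the data". Under Manipulated variables, the control arm answers about people in general rather than about either outgroup.

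**The concern.** Two features of the stated rule act together.

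First, the confirmatory test is conditional on a preliminary check. If the check fails, the article leaves the Hypothesis 1 analysis open, and whatever replaces it is settled with the data and arm labels in view. In a Stage-1 registered report, that is the discretion that registration is meant to remove.

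Second, a planned contrast in a three-group ANOVA ordinarily uses the mean square error pooled over all three groups. The control arm takes no part in the person-first versus identity-first comparison, yet its spread would enter the standard error. Equal spread cannot be presumed, because the control arm rates a different target. The article also expects its means to be the most favorable, on five-point scales with fixed ends. Near-equal arm sizes do not protect this contrast.

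At stake are the true level of the main Hypothesis 1 test and whether that test is defined at all.

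**Working it through.** **Inputs from the article.** Total N = 681, α = .01, power .95, f = .175 (Sample size); five conditions (Manipulated variables); three groups per ANOVA and two-tailed tests (Confirmatory analyses).

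**The article's own figure.** Noncentral F, one-way ANOVA with 3 groups, λ = N·f². The minimum is N = 679, or 3 × 227 = 681 with equal groups, giving power .9507. The stated N is reproduced for three groups. The design has five arms, so the expected arm size is 681 / 5 ≈ 136. What that does to power is a separate matter.

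**Assumptions, not in the article.** 136 per arm, before exclusions; normal data; both descriptor arms with the same SD s; control SD = r·s; contrast error pooled over three arms; the check is Brown-Forsythe at .05.

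**Level of the pooled contrast, ignoring the check.** The true variance of the mean difference is 2s²/n. The pooled error estimates 2s²(2 + r²)/(3n). Hence

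size ≈ 2[1 − Φ(2.576·√((2 + r²)/3))].

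- r = 0.8: (2 + 0.64)/3 = 0.88; √0.88 = 0.938; 2.576 × 0.938 = 2.416; size .0157.
- r = 1.25: (2 + 1.5625)/3 = 1.1875; √1.1875 = 1.090; 2.576 × 1.090 = 2.807; size .0050.

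**With the check applied** (40,000 simulated trials per row):

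| r | Pooled size, no check (formula) | Share passing | Pooled size after a pass | Welch size, no check |
|---|---|---|---|---|
| 0.6 | .0223 | 0 of 40,000 | none passed | .0097 |
| 0.7 | .0189 | 2% | .017 (747 passes) | .0103 |
| 0.8 | .0157 | 32% | .017 | .0102 |
| 0.9 | .0127 | 82% | .013 | .0098 |
| 1.0 | .0100 | 95% | .010 | .0098 |
| 1.1 | .0077 | 83% | .008 | .0101 |
| 1.25 | .0050 | 30% | .006 | .0103 |
| 1.5 | .0022 | 0.4% | too few (143 passes) | .0095 |

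The after-pass sizes carry simulation error. At r = 0.8 there were 12,848 passes, so the standard error is √(.017 × .983 / 12,848) ≈ .001. Across separate simulations the figure ran from about .013 to .017 at r = 0.8, and from .005 to .006 at r = 1.25.

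**Source of the distortion.** With equal arms, a pooled t using only the two descriptor arms held .010. The departure therefore comes from the third arm.

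**Price of the alternative.** With equal SDs and d = .35, power is about .617 for Welch and .621 for the pooled contrast. A second simulation gave .615 and .617.

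**The case against.** **Large distortions do not fit the stated procedure.** A reader might infer from the formula that the true level is about double .01 (.022 at r = 0.6) or a fifth of it (.002 at r = 1.5). The same reader might expect power to drop from .61 to .38 at d = .35 when the arm SDs are .5, .5 and .8. Those figures assume that the pooled contrast runs whatever the checks show. Under the Brown-Forsythe check, the three scenarios pass in none, about 0.3% to 0.4%, and 0.02% to 0.04% of trials. This objection stands. Such figures would matter only if the check were loose enough to let those ratios through, and the article does not say what the check is.

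**The pooled error term and the spreads are inferred.** No error term and no SD appear in the article. Pooling is the default for a contrast in the stated ANOVA, not a commitment. Claims that outcomes will sit at the floor, or that checks will often fail, have no support in the document, and even the direction is open: a less variable control inflates the level and a more variable one deflates it. This stands, so the result is a range.

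**Details may be left to a fuller plan.** An article need not list each diagnostic and threshold, and their absence is no fault. But the article does state the precondition, as the rule for its confirmatory test. The criticism is that an unconditional test is better than this rule.

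**Openness limits discretion.** The Method section commits to releasing data and scripts, so a departure could be seen and re-run. That reduces the harm but does not supply a prespecified test.

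**Conclusion.** The point holds in a moderate form. Under the assumptions listed, the rule has two outcomes when spreads differ. With moderate inequality (control SD 0.8 or 1.25 times that of the descriptor arms) the check passes about 30% of the time, and the contrast then runs at about .013 to .017 or .005 to .006 instead of .01; otherwise it fails and the article gives no test. With larger inequality (0.6 or 1.5) failure is almost certain, and Hypothesis 1 has no test prespecified in the article. Passing the check therefore does not restore the .01 level, and failing it leaves the choice of test to analysts who know the arms.

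The missing fallback can be read directly from the text. The numerical distortion rests on an inferred pooled error term, assumed SDs, 136 per arm and an assumed form of check. Exclusions and simple randomization would make the arms smaller and not exactly equal. The documents do not support saying that the level will in fact be doubled, that power will collapse, or that the checks are likely to fail.

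**What to change.** Replace the conditional sentence under Confirmatory analyses with an unconditional rule:

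- For every outcome and both descriptor pairings, test Hypothesis 1 by the person-first versus identity-first contrast with unequal variances (Welch t, or heteroscedasticity-consistent standard errors), two-sided at .01, with its confidence interval.
- Use Welch's ANOVA for the three-arm comparison.
- Report assumption diagnostics descriptively, with no bearing on which test is used.

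The cost is a sentence or two of text and about 0.2 to 0.4 percentage points of power at d = .35 when spreads are equal. One consequential edit is needed: the Hypothesis 2 paragraph takes partial eta squared from these ANOVAs to set its equivalence bounds, so it should say which effect size it uses once the tests change.

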## Generalizing the person-first language effect

A further concern regarding the use of person-first language that has not been explored systematically pertains to the generalizability of its benefits. In reviewing the literature, it is evident that person-first language does not affect outgroup attitudes and behavioral intentions to the same degree across different social groups. For example, the prevalence of negative implicit associations differed to a moderate extent between participants exposed to the terms "substance abuser" or "person with a substance use disorder" (d = .39; [9]). A moderate-large difference in levels of sympathy or willingness to help was documented when others were described as "addicts" instead of "people with addiction” (d = .61; [10]; see Granello and Gibbs [14] for moderate-large effects when comparing attitudes towards “people with mental illnesses” and “the mentally ill”). Exposure to person-first rather than crime-first language, in turn, led to only a small decrease in perceived recidivism risk of violent offenders (d = .21; [11]). The same study showed that person-first language did not at all impact perceptions of those who had committed nonviolent property or drug offenses ([11]; see Jackl [12] for further small effects comparing person- or crime-first language).

Similarly, St. Louis [13] demonstrated that person-first language evoked more positive outgroup impressions for only two of twelve descriptor pairing–“person with leprosy”/”leper” and “person with psychosis”/”psychotic”. These findings were attained in a diverse sample that included individuals with a language-disorder, parents of clients, speech-language pathology students, and the general public. St. Louis [13] did not elaborate on why person-first language effects were not identified for all descriptor pairings.

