#### Sample size

We aim to recruit *N* = 681 participants. The sample size calculation is based on an a-priori power analysis, considering the smallest effect of interest as a reference [47]. Our goal is to obtain .95 power, with α = .01 (Bonferroni-corrected p-value for five outcomes; see below), to be able to detect also small effects (or differences) of f = .175 with univariate analyses of variance (one-way). We will only recruit participants who are UK residents and older than 18 years. We introduce the former selection criterion (i.e., being a UK resident) as we will apply definitions of disability and violent crime (see Manipulated variables–experimental stimuli) that are provided by UK institutions.

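### The stated .95 power does not apply to the tests that decide Hypothesis 1: at the actual arm size it is about .74 for each three-group ANOVA and .62 (at d = .35) for the person-first versus identity-first contrast

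*Protocol article*

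**What the plan says.** The Sample size section of the protocol article sets the target: "We aim to recruit *N* = 681 participants". The power statement reads "Our goal is to obtain .95 power, with α = .01 (Bonferroni-corrected p-value for five outcomes; see below"), and the effect to be detected is "small effects (or differences) of f = .175 with univariate analyses of variance (one-way").

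The Confirmatory analyses section then makes each ANOVA a comparison of three conditions (identity-first, person-first, control) within one descriptor pairing: "we will conduct five two-tailed ANOVAs" for the disability pairing, and "The analyses will then be repeated for the descriptor pairing" about violent crime. Within each pairing, the language effect is assigned to a contrast: "Planned contrasts will be used to investigate for each descriptor pairing whether average negative outgroup perceptions and affect are lower", and positive perceptions and approach intentions higher, with person-first than with identity-first language. The control is expected to be the most favourable group. The same section closes the matter of power with "We address concerns about the reduced power of the tests by using the corrected p-value of p = .01" in the sample-size calculation.

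The design has five arms (two target groups by two descriptors, plus one control), filled by simple randomization. The introduction reports that, in an earlier study, person-first language "led to only a small decrease in perceived recidivism risk of violent offenders (d = .21; [11").

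**The concern.** Hypothesis 1a-e is about person-first against identity-first language. The effect size used for planning, f = .175, describes the spread of three means, one of which is the control. Ratings of most people may differ widely from ratings of either outgroup, so an omnibus F can be significant because of the control arm alone and say nothing about language. The article gives no power for the contrast that does address language, yet it presents the power question as settled.

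The number of participants adds to the problem. Each test uses only the arms of one pairing plus the control, not the whole sample. If .95 belongs to neither the omnibus test nor the contrast, a non-significant Hypothesis 1 result will look more informative than it is.

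**Working it through.** **Inputs from the protocol article.** N = 681, power .95, alpha .01 and f = .175 (Sample size); five arms (Manipulated variables); three groups per ANOVA, two-tailed (Confirmatory analyses); d = .21 (Generalizing the person-first language effect). **Assumptions.** Equal allocation, so 681/5 = 136.2 per arm. The contrasts are tested at two-sided .01 unless stated otherwise.

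**1. Reproducing 681.** For a one-way ANOVA with k groups, the noncentrality is f²N with k − 1 and N − k degrees of freedom, and f² = .175² = .030625. With k = 3 the smallest N for .95 power at alpha .01 is 679. Rounded up to equal groups this is 681 = 3 x 227, with power .951. Other group counts do not give 681: k = 2 needs 586, k = 4 needs 747, and k = 5 needs 802. So 681 is the total for one three-group ANOVA.

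**2. The omnibus test as it will be run.** Three of five arms hold 3 x 136.2 = 408.6, about 409 participants. The noncentrality is .030625 x 409 = 12.5, against 20.9 at 681. Power at f = .175 and alpha .01 is .74.

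**3. The contrast.** Noncentral t with noncentrality d√(n/2) = d√68.1 = 8.25d and 3n − 3, about 406, degrees of freedom. This gives 2.89 at d = .35 and 1.73 at d = .21, against a two-sided .01 critical value of about 2.59.

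| Per arm | Level | d = .35 | d = .21 |
|---|---|---|---|
| 136.2 | two-sided .01 | .618 | .198 |
| 136.2 | one-sided .01 | .710 | .275 |
| 136.2 | two-sided .05 | .822 | .409 |
| 227 | two-sided .01 | .874 | .365 |

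The value d = .35 is 2f, the two-group conversion, and is not printed in the article. The value d = .21 is printed, but for perceived recidivism risk, which is not an outcome here.

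**4. What f = .175 implies for the contrast.** With unit SD, f² is the mean squared deviation of the three group means. Take the expected order: identity-first at 0, person-first at d, control at d or beyond.
- Control equal to person-first: f = d√2/3, so d = 3 x .175/√2 = .371. This is the maximum; power is .68.
- Equal spacing: f = d√(2/3), so d = .175 x √1.5 = .214. Power is .21.
- Person-first equal to identity-first: d = 0. The control carries all of f.

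**5. What would be needed.** At 136.2 per arm and two-sided .01, power reaches .95 only at about d = .51. For .95 power at d = .35 about 292 per arm are needed (5 x 292 = 1,460), and at d = .21 about 810 (5 x 810 = 4,050).

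**6. Exclusions.** The target is a recruitment figure, and participants who fail checks or belong to a target group are removed. No rate is given. If 20% were lost, the base figures would fall from .62 and .20 to about .50 and .15.

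**The case against.** Several points in the plan's favour stand. The protocol already assigns the language comparison to planned contrasts, so it does not decide Hypothesis 1 on the omnibus F. The alpha and sidedness of the contrasts are not stated: the Bonferroni adjustment is attached to the ANOVAs and the contrasts are worded directionally, so a more lenient level is arguable. Neither d = .35 nor d = .21 is a declared design effect. Part of the shortfall also comes from spreading 681 over five arms rather than from omnibus versus contrast: at d = .35 the contrast would have power .87 with 227 per arm. None of this restores .95, because every variant in the table falls below it.

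A reader might infer more than the document supports.
- *That a null contrast for violent crime would be counted as support for Hypothesis 2.* The plan does not do this. Hypothesis 2 depends first on a paired t-test of attitude importance and then on equivalence tests with bounds taken from the disability effects.
- *That the Bonferroni divisor should be ten because the five ANOVAs are run twice.* The plan defines its family as the five ANOVAs within a pairing, and .05/5 = .01 is right for that family. It makes no claim of 5% across both pairings.
- *That a pooled descriptor main effect is the necessary remedy.* With about 272 against 272, it has power .93 if d = .35 holds in both pairings. But Hypothesis 2 predicts unequal effects: power is .75 if they are .35 and .21 (average .28), and .29 if they are .35 and 0 (average .175).

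**Conclusion.** The concern holds in this form: the .95 power stated at f = .175 applies neither to the three-group ANOVAs that will be run nor to the contrast that answers Hypothesis 1. Omnibus power is about .74. Contrast power at two-sided .01 is .62 at d = .35 and .20 at d = .21, and it cannot exceed about .68 for any pattern with f = .175 in the expected order. These figures rest on equal allocation and no exclusions; exclusions would lower them. The d values are benchmarks, not the plan's own design effects for the contrast. The choice of alpha or sidedness changes the size of the gap but does not close it at d = .35 or d = .21. The finding concerns the stated power. It does not show that the Hypothesis 2 decision or the per-pairing multiplicity rule is wrong.

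**What to change.** In Sample size and Confirmatory analyses:

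1. Withdraw the .95 claim for Hypothesis 1.
2. State power for the person-first versus identity-first contrast, and for the three-group omnibus test, at the actual per-arm number (about 136 before exclusions). Give the contrast's smallest effect of interest as d.
3. State the alpha and sidedness of the contrasts.
4. State that Hypothesis 1 is judged on the contrast and that a significant omnibus F alone does not support it.

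If N stays at 681, this is a change of wording only. The cost is a less favourable stated power, with .95 reached only near d = .51 at two-sided .01. Keeping .95 for a smaller contrast would need a larger sample, about 1,460 for d = .35. A pooled descriptor main effect may be added as a supplement, with its power shown under unequal effects, but it is not required. As a stage-1 report with no data collected, the text can still be changed.
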